### Control Group

The Control Group will receive access to a static (ie, noninteractive) FASD resource Web page within IRIS that provides a list of recommended book titles, videos, websites, and organizations.

Participants in the Control Group receive a Mid-Study Progress Message approximately 10 weeks after randomization (coinciding with the SF Intervention Group’s mid-program progress report). The message thanks participants for taking part in the study, encourages them to visit the static resource page, and reminds them of the 5-Month Follow-up Assessment.

Participants in the Control Group will gain access to the Strongest Families FASD program (without coaching) after their study participation is complete. The program is designed to be self-directed and contains built-in tutorials to help users navigate the website, though technical support is available. The Strongest Families program will be accessible until 6 months after the last Control Group participant receives access to the website.

### Follow Up Assessments

Participants will complete follow-up assessments at 5 and 11 months post-randomization. Participants in both study groups will receive an email message at 145 days (for the 5-month assessment) and 325 days (for the 11-month assessment) prompting them to complete the appropriate follow-up assessments online within IRIS. The assessments will take approximately 20-30 minutes in total to complete. Participants will be asked to complete the DASS-21 and the CBCL and to update some demographic information (eg, child’s medications, any new diagnoses). Up to 3 email reminders will be sent and a courtesy phone call reminder will be made for incomplete assessments approaching their expiry date. For each completed follow-up assessment, participants will receive a US $25 gift card by mail or online and a summary of their assessment results via email (within IRIS).

Assessment Results Letters (baseline and follow-ups) will report if the child’s CBCL scores fall within the clinical range for the Anxious/Depressed (CBCL 1½-5 & 6-18), Withdrawn/Depressed (CBCL/6-18), or Withdrawn (CBCL/1½-5) scales and will also include the parent’s depression, anxiety, and stress scores (DASS-21) as compared to the general population (ie, about the same, higher, or much higher than most people). Additionally, the child’s Externalizing CBCL scores will be reported as being the same, improved, worse, or resolved (within the normal range) as compared to baseline. Letters will emphasize to the participant that assessment results are not a diagnosis and do not replace medical care. Participants will be able to request a phone call from study staff to discuss assessment results.

### Statistical Analyses

Data will be analyzed by a statistician blinded to group assignment. The study design is a 2 (group: intervention vs control) × 3 (time: baseline, 5 months, 11 months) mixed factorial with repeated measures.

An intention-to-treat analysis will be performed using a full information maximum likelihood [31] mixed-effects regression framework. Specifically, for the primary outcome of the study we will create a hierarchical (“stacked”) data set and regress the CBCL externalizing scores on group (coded as Control=0 and Intervention=1), time (coded naturally as baseline=0, 5 months=5, etc) and the group × time interaction. Child age, sex, comorbidities, and medications have been identified a priori as variables to be added to the model. The critical test will be the group × time interaction. Based on the described coding, the parameter for this effect will be the estimated differential change on the CBCL externalizing score between the control and intervention groups per month. The overall effect will be this parameter estimate × 5. We anticipate using an unstructured covariance matrix for deriving the error term.

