##  Methods

### Study Design

This study is a 2-arm randomized controlled trial comparing participants assigned to receive either the Strongest Families FASD Web-based parent-training program (SF Intervention Group) or a static resource Web page (Control Group). Neither group will be restricted from accessing additional programs or services during study participation. The Consolidated Standards of Reporting Trials (CONSORT) recommendations [17] are used to guide the methodology. Details of the study design are illustrated in Figure 1. The study has been approved by the Queen’s University Health Sciences & Affiliated Teaching Hospitals and IWK Health Centre Research Ethics Boards. The primary and secondary outcome measures will be administered to all participants at baseline (pre-randomization), 5 months, and 11 months post-randomization. The Client Satisfaction Questionnaire (CSQ-8) and Strongest Families Program Satisfaction Questionnaire: FASD Version will be administered to the SF Intervention Group upon completion of the program. Study participation ends for participants in both study groups after completing the 11-Month Follow-up Assessment.

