### Sample

A sample of 200 parents of children with FASD, aged 4-12 years, will be recruited into the study. Our sample size estimate was based on the minimal clinically important difference in change in outcomes from 0 to 5 months. We have expressed this effect size as a moderate (d=0.50; ie, one half a standard deviation) difference in reduction on CBCL externalizing score for intervention group compared to control. Setting our Type I error rate (alpha) at 0.05. Thus, we require 85 participants in each group for a power of 0.90 and a total sample size of 170 (we will recruit 200 to account for losses). It is reasonable to expect this effect given the larger effects seen in children with oppositional defiant disorder and attention-deficit hyperactivity disorder [12]. The age range for the sample was chosen because interventions provided at this stage can help to prevent the development of secondary problems and because parent-training methods have been most highly developed for this age group [27]. The target sample size is attainable based on the strong relationships we have with FASD diagnostic clinics and FASD support groups across Canada.

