#### Eligibility Screening (Phase 2)

Phase 2 screening involves completion of the CBCL baseline measure to determine eligibility for randomization. DASS-21 scores will not impact eligibility. All participants who complete the baseline assessment receive a US $25 gift card by mail or email (their choice).

The following criteria must be met in order for participants to be randomized into a study group:

CBCL Externalizing t-Score ≥64 (clinical range);Parental report of a formal diagnosis of one of the following disorders captured under the umbrella term FASD: Fetal Alcohol Syndrome (FAS); partial fetal alcohol syndrome; alcohol related neurodevelopmental disorder; static encephalopathy (alcohol exposed); neurobehavioral disorder (alcohol exposed); and other (To determine possible valid diagnoses not included on our predefined list, parents may report an “other” diagnosis that they believe falls under the umbrella term FASD. These diagnoses will be confirmed by the co-principal investigator on a case-by-case basis and will be accepted if the diagnosis identified (a) has been provided by a recognized FASD diagnostic clinic and (b) conforms to one of the recognized diagnostic schemes used in the assessment of children suspected of having an FASD.);Meets the following criteria for behavior suggestive of FASD adapted from the Neurobehavioral Screening Tool (NST) [28,29]: (a) For children age 6-12 (CBCL/6-18), participants must endorse 7 out of 8 of the items listed in Table 1; or (b) For children age 4-5 (CBCL/1½-5), participants must endorse 3 out of 5 of the items listed in Table 1 with at least 2 endorsements from the items marked with an asterisk.No suicide attempts within the previous 6 months for children 6-12 years of age (screened for using the CBCL/6-18 only); andNo current risk of suicide attempts for children 6-12 years of age (screened for using the CBCL/6-18 only).

**Table 1 table1:** Parent endorsements required to meet clinical eligibility criteria.

CBCL Item	CBCL/1½-5	CBCL/6-18
Acts young for age	✓	✓
Can’t concentrate or poor attention*	✓	✓
Can’t sit still, restless, hyperactive*	✓	✓
Disobedient at home*	✓	✓
Doesn’t show guilt after misbehaving	✓	✓
Argues a lot		✓
Impulsive or acts without thinking		✓
Lying or cheating		✓

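### The primary model estimates a baseline group difference that randomization sets to zero and does not adjust for baseline CBCL, at a modest cost in precision

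*Protocol article*

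**What the plan says.** In the protocol article, Statistical Analyses describes a stacked data set and a mixed-effects regression by full information maximum likelihood. For the primary outcome the plan is to "regress the CBCL externalizing scores on group (coded as Control=0 and Intervention=1), time" and the group × time interaction. Time is coded in months, with baseline as 0. The interaction is the critical test, its coefficient × 5 is the overall effect, and the covariance matrix is expected to be unstructured. The covariates named in advance are child age, sex, comorbidities and medications.

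Study Design fixes when the score is taken: "The primary and secondary outcome measures will be administered to all participants at baseline (pre-randomization), 5 months, and 11 months post-randomization". Eligibility Screening (Phase 2) makes the same score an entry criterion, "CBCL Externalizing t-Score ≥64 (clinical range", so every randomized family has a baseline value.

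The Sample section bases the size on the "minimal clinically important difference in change in outcomes from 0 to 5 months", set at half a standard deviation. It concludes that "we require 85 participants in each group for a power of 0.90 and a total sample size of 170".

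**The concern.** With baseline coded 0, the coefficient of group is the difference between the arms at baseline. That visit comes before randomization, so the true value is zero, yet the model estimates it freely. Every departure of the observed baseline difference from zero is then subtracted in full from later differences.

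Only part of a chance baseline difference persists to follow-up, because the regression slope of follow-up on baseline is normally below 1. Subtracting all of it over-corrects. An arm that happens to start worse appears to improve more, and the estimate is noisier than it need be. Age, sex, comorbidities and medications, entered as main effects, do not replace the baseline score.

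What is at stake is precision on the primary outcome, and how far the reported effect depends on a chance imbalance. Validity is not at stake.

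**Working it through.** **1. The plan's own figure.** Inputs from the Sample section: d = 0.50, alpha 0.05, power 0.90. Sidedness is not stated; two-sided is assumed here because one-sided would give 69.

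n per arm = 2(1.960 + 1.282)² / 0.50² = 84.1, rounded up to 85. Power at 85 is Φ(0.50·√(85/2) − 1.960) = 0.903. With 15% losses, 170/0.85 = 200. The figures reproduce as a plain comparison of two means, with no credit taken for baseline adjustment.

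**2. General result, two waves.** Let the baseline and follow-up SDs be SD0 and SD1, with correlation r.

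- var(change) = SD0² + SD1² − 2r·SD0·SD1
- var(adjusted) = SD1²(1 − r²)
- difference = (SD0 − r·SD1)² ≥ 0

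In large samples adjustment is never less precise. With equal SDs the ratio of adjusted to change variance is (1 + r)/2.

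**3. Allowing for the entry cut.** The protocol gives neither r nor the score distribution, so these are assumptions: source population mean 66–70, SD 8–10, correlation ρ = 0.6–0.8 before the cut, equal SDs before the cut. Selecting on baseline leaves the slope of follow-up on baseline at ρ. It reduces the baseline variance to a fraction k of its source value. In units of the source variance:

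- var(adjusted) = 1 − ρ²
- var(change) = (1 − ρ²) + (1 − ρ)²·k

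| Mean, SD, ρ | k | Adjusted | Change | Ratio | Power at 85 per arm |
|---|---|---|---|---|---|
| 70, 8, 0.6 | 0.556 | 0.640 | 0.729 | 0.878 | 0.936 |
| 68, 8, 0.7 | 0.486 | 0.510 | 0.554 | 0.921 | 0.925 |
| 66, 10, 0.8 | 0.409 | 0.360 | 0.376 | 0.957 | 0.915 |

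Power is Φ(0.50·√(85/(2·ratio)) − 1.960), reading d = 0.50 as SDs of change; the protocol does not say which SD is meant. Trial simulation at ρ = 0.6 and 0.7 gave 0.91–0.93 adjusted against 0.89–0.91 unadjusted, with the same mean estimate.

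**4. The model as written.** The tested quantity is a linear slope over months 0, 5 and 11, × 5. Generalized least squares for that model, with compound symmetry before the cut and the same truncation, gives weights of about −0.45, 0.00 and +0.45 on the three visits. It is thus close to the 0–11 month change scaled by 5/11. Constraining the baseline difference to zero gives a variance ratio of 0.87–0.96 against the free model, so the gain carries over from the two-wave case.

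**5. Chance imbalance.** A baseline difference of 1 T point moves a 0–5 month change estimate by (ρ − 1) = −0.4 to −0.2 points. In the planned slope × 5 contrast the shift is about 0.45(1 − ρ), or 0.09–0.18 points. Under these assumptions the baseline SD after the cut is about 5.2–7.2. The standard error of the baseline difference at 85 per arm is that SD × √(2/85), or 0.8–1.1 points. A typical shift in the 0–5 month change is therefore about 0.2–0.4 points, in either direction.

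**The case against.** The strongest reply is that group × time with baseline among the outcomes is a standard and valid analysis, in a trial already sized at 90% power for change. That stands. A reader might infer that the estimate is biased or the sample size wrong; neither follows. The estimate is unbiased over randomizations, its ordinary standard error already includes the imbalance, and 85 per arm reproduces.

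Four other stronger readings are tempting and are not supported.

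- **Textbook savings.** With equal SDs, (1 + r)/2 gives 25% at r = 0.5 and 15% at r = 0.7, as if 170 families were worth 170/0.75 = 227 or 170/0.85 = 200. The T≥64 rule narrows the baseline spread and makes equal SDs implausible here.
- **The entry cut as the cause.** Selection on baseline does not change the slope. It shrinks the baseline variance and so reduces the gain.
- **A simple 5-month change score.** The test is on a linear slope, and the 5-month visit carries almost no weight. The power figures for the 0–5 month comparison show the size of the gain; they are not the power of the planned test.
- **Loss on the secondary outcomes.** The model is stated for the primary outcome only. The article does not say how internalizing, DASS-21 or social competence scores will be analysed.

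What remains is that the article does fix the model terms, the time coding, the critical test and the covariate list. That specification leaves a completely observed baseline score unused as an adjuster.

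**Conclusion.** The point holds as a modest loss of efficiency, and of accuracy given the observed baseline, in the stated primary model. Under the assumed distribution, adjustment saves about 4–13% of the variance. At 85 per arm that is roughly one to three percentage points of power, from about 0.90 to about 0.91–0.93, with the most favourable assumptions slightly above.

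The size depends on a correlation, mean and SD that the protocol does not give. The direction does not: in large samples the gain cannot be negative. The change is worth making because it costs almost nothing, not because the plan is invalid.

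**What to change.** **Preferred.** Drop the group main effect and keep time and group × time, so both arms share one baseline mean. Baseline stays in the outcome vector, the critical test and the × 5 formula stay as they are, one parameter fewer is estimated, and all randomized families remain in the likelihood. The cut baseline is still modelled as a normal outcome, as it already is in the plan.

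**Alternative.** Use baseline CBCL as a covariate for the 5- and 11-month scores, with its own coefficient at each visit. This avoids a normal model for the cut baseline but costs more. Baseline must leave the outcome vector. The critical test and the × 5 formula must be rewritten as group contrasts at follow-up, because group × time would then compare only months 5 and 11. Families with no follow-up would contribute nothing.

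Either form uses data already collected and should be fixed in writing before unblinding, so that the choice cannot look data-driven. If the secondary outcomes are to use the same model form, make the same change there, each with its own baseline.

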### Intervention Group

The online Strongest Families FASD program is provided to the parent with weekly telephone coaching sessions; there is no contact with the child. The program consists of evidence-based parenting strategies provided in 11 online sessions using easy-to-read text, demonstrative video and audio clips, interactive questionnaires, and practice exercises. Participants enter information (eg, child’s name and specific behavior problems) into IRIS to customize the program content. The weekly coaching sessions facilitate skill acquisition and successful implementation using problem-solving and role-playing techniques. Supplementary program materials (eg, Reward Chart, a Daily Strengths Chart, a Visual Schedule Template, Tryout Pages, and Tips for Teachers Information Sheet) are sent to participants via mail. These materials are provided in physical format to enable parents to post the materials in a convenient place in the home and to facilitate communication between home and school or day care. A booster telephone coaching session is offered 1 month after completion of the program to check in with the parent to review consistent use of the skills, prevent or deal with setbacks, and provide support and encouragement, if needed. An experienced coach supervisor will conduct weekly case review with coaches to problem-solve and to review quality assurance and adherence to protocols.

The effectiveness of the principal components of the intervention has been supported in previous studies [13-15] and are currently being used by the SFI Service Program. The content was revised to tailor the intervention to the needs and challenges specific to families affected by FASD. Changes were informed by data collected in a series of telephone interviews with families and clinicians who have personal and professional interest and expertise in the field [30].

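### The primary test is a linear slope over months 0, 5 and 11, with slope × 5 as the effect, but the trial was sized on the change from 0 to 5 months

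*Protocol article*

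**What the plan says.** Under Statistical Analyses, the protocol article calls the design a "2 (group: intervention vs control) × 3 (time: baseline, 5 months, 11 months) mixed factorial with repeated measures". It then specifies the primary model: regress the score on group, on "time (coded naturally as baseline=0, 5 months=5, etc") and on their product. The product term is the critical test. Its coefficient is described as a between-group difference in change per month, and "The overall effect will be this parameter estimate × 5". An unstructured error covariance is anticipated.

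Under Sample, the calculation rests on the "minimal clinically important difference in change in outcomes from 0 to 5 months", expressed as a "moderate (d=0.50; ie, one half a standard deviation) difference in reduction on CBCL externalizing score for intervention group compared to control". From this it concludes that "we require 85 participants in each group for a power of 0.90 and a total sample size of 170 (we will recruit 200 to account", the extra 30 being the allowance for attrition.

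On timing, Intervention Group says: "The program consists of evidence-based parenting strategies provided in 11 online sessions". Coaching is weekly, and one booster call is offered a month after completion. Control Group places the mid-program report at about 10 weeks after randomization.

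**The concern.** The sample size and the primary analysis address different quantities. One is the between-group difference in change at month 5. The other is a straight-line rate of separation fitted through month 11 and rescaled to five months. They agree only if the arms separate at a constant monthly rate for the whole 11 months.

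For a program delivered over roughly the first five months, a gain by month 5 that is then kept, or partly lost, is at least as plausible. In that case the headline figure would be smaller than the 5-month difference the trial was built to detect. A program that met the protocol's own minimal clinically important difference could be reported as falling well short of it. The stated power would also not be the power of the test performed.

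**Working it through.** **Inputs from the article.** Alpha 0.05, d = 0.50 in SDs of the 0-to-5-month change, power 0.90, 85 per group (Sample); visits at 0, 5 and 11 months, numeric time, one slope, effect = slope × 5 (Statistical Analyses). The article does not state sidedness; two-sided reproduces its figure (one-sided would give 69).

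**Assumed.** Correlations, SDs and the shape of the effect over time, because the article gives none.

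**1. The stated sample size.** n per group = 2(1.960 + 1.282)² / 0.50² = 84.06, so 85. Power at 85: 0.5 × √(85/2) = 3.26, and Φ(3.26 − 1.96) = 0.903 (0.900 by the t test). The figure is right for a comparison of 0-to-5-month change.

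**2. What slope × 5 estimates.** Let D0, D5 and D11 be the between-group differences at the three visits. The mean time is 16/3 = 5.333. The deviations are −5.333, −0.333 and 5.667, with sum of squares 60.667. Under equal variances and correlations:

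slope × 5 = −0.440·D0 − 0.027·D5 + 0.467·D11.

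With D0 = 0, D5 = d and D11 = f·d, the recovered fraction is −0.027 + 0.467f. It equals 1 only at f = 11/5 = 2.2.

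**3. Power of the slope test, equal correlation, 85 per group.** Let σ be the residual SD within child. Then d = 0.5 × √2 × σ = 0.707σ. For a held effect the slope is 0.0879 × 0.707σ = 0.0622σ. Its standard error is σ√(2/(85 × 60.667)) = 0.0197σ. The ratio is 3.16, so power is Φ(3.16 − 1.96) = 0.88. For other shapes the ratio scales with the recovered fraction.

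| Difference at month 11 | slope × 5, as a fraction of d | Power |
|---|---|---|
| 2.2d (constant divergence) | 1.00 | near 1.00 |
| 1.05d | 0.46 | 0.914 |
| d (held) | 0.44 | 0.88 |
| 0.75d | 0.32 | 0.64 |
| 0.50d | 0.21 | 0.32 |
| 0 | −0.03 | 0.05 |

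**4. Other covariances, held effect.** The same calculation by generalized least squares. Correlations are listed as (0,5), (0,11), (5,11), with unit variances unless stated.

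| Assumed covariance | slope × 5, as a fraction of d | Power |
|---|---|---|
| 0.50, 0.45, 0.75 | 0.31 | 0.63 |
| 0.60, 0.50, 0.75 | 0.34 | 0.62 |
| 0.70, 0.50, 0.70 | 0.42 | 0.65 |
| Decaying with time, 0.6 to 0.8 per 5 months | 0.45 | 0.71 to 0.65 |
| 0.70, 0.50, 0.60 | 0.49 | 0.77 |
| 0.75, 0.50, 0.55 | 0.54 | 0.81 |
| 0.80, 0.50, 0.50 | 0.60 | 0.84 |
| Baseline SD 0.7, equal correlation 0.5 | 0.48 | 0.93 |

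Simulated maximum likelihood fits with an unstructured covariance (300 runs per scenario) gave fractions of 0.34 to 0.54 with complete data. With 100 per group, 15% missing at month 5 and 30% missing at month 11, they gave 0.38 to 0.59.

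**5. When the program ends.** A mid-program report at about 10 weeks implies completion at about 20 weeks, or 140 days. The 5-month assessment prompt goes out at 145 days (Follow Up Assessments). The booster call follows about a month later.

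**The case against.** The 2 × 3 factorial description could be read as time with three levels. That reading does not survive the rest of the paragraph: numeric coding, one coefficient per month and multiplication by 5 describe a straight line. The unstructured covariance concerns the errors, not the mean.

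The article speaks of an overall effect and never labels it the 5-month effect, nor does it name a primary time point. This stands. The 5-month target is inferred from the sample-size basis and from the multiplier itself.

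A reader might infer more than the article supports:

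- That the effect is always understated by more than half. This holds under equal or decaying correlation, but the planned covariance is unstructured, and some patterns recover 0.54 to 0.60.
- That the 5-month data always carry a negative weight. This too depends on the covariance; with correlations 0.80, 0.50, 0.50 the weight is +0.27.
- That power is badly reduced in every case. A held effect has 0.88 under equal correlation and 0.93 with a smaller baseline SD. A smaller baseline SD is possible given entry at T ≥ 64, although the article gives no SD.
- That a plateau or fade is a documented fact. It is not. Families who lose contact are put on hold and invited to resume, so some may be treated after month 5. Both arms may also use other services.

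None of this supplies a reason to expect constant divergence to month 11.

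**Conclusion.** The point holds in this form: the article pairs a sample size for the 0-to-5-month difference with a primary test and estimate that match it only under constant divergence to month 11, a shape it does not justify.

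For an effect held from month 5, slope × 5 recovers about 0.3 to 0.6 of the 5-month difference. Under equal correlation, a true d of 0.50 would appear as 0.44 × 0.50 = 0.22. Under the same correlation, a fade to 75% or 50% lowers recovery to 0.32 or 0.21.

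The 0.90 power was not calculated for this test. With 85 per group and a held effect, power runs from about 0.62 to 0.93 over the covariances tried, so it may be materially lower or slightly higher than stated. A fade to 75% or 50% gives 0.64 or 0.32 under equal correlation.

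The size of the shortfall rests on assumed covariances and shapes. The mismatch itself does not. Because it affects the primary test and the headline estimate, it should be corrected before the analysis.

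**What to change.** Before unblinding, change the Statistical Analyses section as follows:

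- Keep the full information maximum likelihood model and the unstructured covariance, but enter time as a three-level factor.
- Declare the group × 5-month contrast, that is the between-group difference in change from baseline to 5 months, as the primary test and estimate.
- Report the group × 11-month contrast as secondary.
- Delete the × 5 rule.

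The 5-month estimate is then the 5-month difference whatever happens afterwards, and 85 per group with power of about 0.90 applies to the test performed.

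The cost is wording only, with no new data, but the change is not free in power. Under equal correlation the slope test is already the stronger one if the 11-month difference is 1.05 times the 5-month difference (0.914 against 0.903). With a smaller baseline SD it can be stronger even for a held effect (0.93). It would therefore be wrong to assume that power is lost only if the effect grows linearly for all 11 months. If the sponsor does want a slope over 11 months as the target, the article should say so, justify the linear shape, and recalculate power for that test.

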### Randomization and Allocation

Random allocation to the intervention or control group in 1:1 ratio was established independently by an external researcher using a permuted blocked randomization procedure. The external researcher concealed the group placements in sequentially numbered, sealed double envelopes to maintain blinding of study staff. Envelopes are opened sequentially by the coordinator (or delegate) and only after the enrolled participants complete the baseline assessments and are deemed eligible.

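### The primary model and the sample size make no allowance for shared telephone coaches in the intervention arm; if outcomes correlate within coach, the standard error is too small and power is below 0.90

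*Protocol article*

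**What the plan says.** Families are randomized individually: "Random allocation to the intervention or control group in 1:1 ratio" (Protocol article, Randomization and Allocation).

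The intervention arm works through 11 online sessions with weekly telephone coaching. Under Intervention Group, coaching is described as an active ingredient: "The weekly coaching sessions facilitate skill acquisition and successful implementation using problem-solving and role-playing techniques". The same section shows that there is more than one coach: "An experienced coach supervisor will conduct weekly case review with coaches". The Introduction adds that coaches log in to the IRIS platform to follow each parent's activity. Under Control Group, controls receive a fixed online resource list and no coaching.

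Statistical Analyses sets out a mixed-effects regression of the CBCL externalizing score on group, time and group × time, with child age, sex, comorbidities and medications as further terms. On the error structure it says: "We anticipate using an unstructured covariance matrix for deriving the error term". No coach term is named. The section also says that the statistician is blinded to group.

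The Sample section sizes the trial on a "moderate (d=0.50; ie, one half a standard deviation) difference in reduction on CBCL externalizing score", with "Setting our Type I error rate (alpha) at 0.05", and concludes that "we require 85 participants in each group for a power of 0.90". The 30 families recruited beyond 170 are there to cover losses.

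**The concern.** Provider clustering can arise in one arm only, so this is a partially nested design. Families with the same coach may do better or worse together, because coaches differ in skill or style. The unstructured matrix for the stacked three-visit data allows for correlation among one child's measurements. It leaves different families independent, including those with the same coach.

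Any positive within-coach correlation would therefore make the planned standard error of the group × time effect too small and the confidence interval too narrow, and the stated power would be too high. The error runs in one direction, towards overstating the precision of the intervention effect. The Conclusions section says that the trial should inform eHealth policy and uptake of the program, so the interval ought to reflect variation between coaches.

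**Working it through.** **Inputs from the protocol article (Sample; Randomization and Allocation).** d = 0.50 with SD = 1, alpha 0.05, power 0.90, 85 per group, 170 in total, 200 recruited, allocation 1:1. Sidedness is not stated.

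**The plan's own figure.** With independent families and a two-sided test, n per group = 2 × (1.960 + 1.282)² / 0.50² = 84.1, rounded up to 85. Power at 85 is 0.903 by the normal approximation and 0.900 by the noncentral t. A one-sided test would need 69, so the plan is two-sided. Allowing 15% loss, 170 / 0.85 = 200. The stated figures are reproduced exactly, and nothing is left over for clustering.

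**Assumed inputs.** The article gives neither the number of coaches K nor the ICC. The ranges are K = 3, 5, 8 and ICC = 0.01, 0.02, 0.05 on change, with 85 analysed families per arm and equal caseloads.

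**Formulas.**
- Caseload: m = 85 / K
- Design effect, intervention arm only: DE = 1 + (m − 1) × ICC
- True SE = √[(1 + DE) / 85]; naive SE = √(2 / 85)
- Ratio R = true / naive = √[(1 + DE) / 2]; share by which the naive SE is understated = 1 − 1/R
- Power of a test using the true SE = Φ(0.50 / true SE − 1.96)
- Type I error of the naive test = 2 × [1 − Φ(1.96 / R)], if coach effects vary around a mean of zero

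**Results.**

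| K | m | ICC | DE | R | Naive SE understated | Type I error | Power |
|---|---|---|---|---|---|---|---|
| 3 | 28.3 | 0.01 | 1.27 | 1.066 | 6% | 0.066 | 0.864 |
| 3 | 28.3 | 0.02 | 1.55 | 1.128 | 11% | 0.082 | 0.823 |
| 3 | 28.3 | 0.05 | 2.37 | 1.297 | 23% | 0.131 | 0.710 |
| 5 | 17.0 | 0.01 | 1.16 | 1.039 | 4% | 0.059 | 0.880 |
| 5 | 17.0 | 0.02 | 1.32 | 1.077 | 7% | 0.069 | 0.857 |
| 5 | 17.0 | 0.05 | 1.80 | 1.183 | 15% | 0.098 | 0.787 |
| 8 | 10.6 | 0.01 | 1.10 | 1.024 | 2% | 0.056 | 0.890 |
| 8 | 10.6 | 0.02 | 1.19 | 1.047 | 4% | 0.061 | 0.876 |
| 8 | 10.6 | 0.05 | 1.48 | 1.114 | 10% | 0.078 | 0.833 |

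Worked line for K = 3, ICC = 0.05: DE = 1 + 27.33 × 0.05 = 2.37; R = √(3.37 / 2) = 1.297; true SE = √(3.37 / 85) = 0.199; 0.50 / 0.199 − 1.96 = 0.55, so power is 0.71.

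At ICC = 0, DE = 1 and R = 1, and the plan's figures stand. These are normal approximations. With few coaches, the loss of degrees of freedom would lower power further.

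**The case against.** **Sharing and correlation are not documented.** The article gives no coach count, caseload, assignment rule or ICC. A reader might infer that the standard error is certainly too small, but the documents do not support that. Sharing is a strong inference: avoiding it would take roughly one coach per family for about 100 families. A positive ICC is not shown at all. Standardized online content, weekly review of adherence, and no contact between coach and child all point towards a small one. This stands, and it is why the point is conditional.

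**Type I error.** A reader might also infer that the false-positive rate must exceed 0.05. Coaches act only after randomization and only through the intervention. If the program, coaching included, does nothing for any family, coaches add no correlation and the rate stays near 0.05. The inflated figures require coach effects that differ but average zero, and inference to a wider population of coaches. This also stands. The loss of precision and power does not depend on the zero-mean condition.

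**Size.** A ratio of 1.30 might be read as a standard error understated by 30%. It means that the true value is 30% larger, so the naive one is understated by 23%. That end of the range comes from one corner, 3 coaches with ICC 0.05.

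**An analysis plan not shown could add a coach term.** The quoted sentence on covariance is also provisional. This has some force, but the article lists the model's terms and error structure without a coach level, and its sample size reproduces only under independence.

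**Conclusion.** The concern holds in conditional form. The primary model and sample size treat all families as independent, while one arm receives an active component from a team of coaches. If outcomes correlate within coach, the standard error of the group × time effect is understated and power is below the stated 0.90.

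Under the assumed 3–8 coaches and ICC 0.01–0.05, with 85 families per arm, the effect runs from negligible (true standard error 2% larger, power 0.89) to material (30% larger, power 0.71). The matching type I error range of 0.056–0.13 applies only if coach effects vary around zero. The ranges are assumptions, and nothing in the article locates the trial within them. The change is worth making because it is cheap and the possible error favours the intervention.

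**What to change.** 1. Record which coach served each family. Coaches work in IRIS, so this should be retrievable. Report the number of coaches and their caseloads.
2. Prespecify a partially nested analysis: a coach random effect in the intervention arm only, on change from baseline, with small-sample degrees of freedom. Make it at least a sensitivity analysis of the primary result.
3. If there are too few coaches to estimate the variance, report the primary interval with the standard error inflated over ICC 0.01–0.05, labelled as assumed values.
4. State in the Sample section that the 0.90 power assumes no coach clustering.

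The cost is modest analysis work and no change to design or recruitment. There are two downsides. The interval will be somewhat wider and, with few coaches, the coach variance will be imprecisely estimated. A coach code present in one arm only also reveals allocation to the blinded statistician, so this analysis should be run after the blinded primary analysis is locked.
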